### Cooking intervention

The 6-week cooking intervention (TP_1_) in phase 2 will be delivered by a chef who is professionally trained, licensed, and certified regarding local food safety regulations. The intervention site will be a community-based kitchen site located within ward 7 or 8. Participants will be divided into two groups of 15. Each group will meet weekly at the kitchen site for a 90-min culinary education session. There will be no group assignment; participants may choose which group to attend, but can only attend one group session per week. The minimum number of participants required for delivery of the intervention will be one participant per session. In case of the need for an emergency medication administration for unknown food allergies, all sessions will be staffed with clinical research team members. Medical students trained in culinary medicine will also be present during each session to assist participants as needed. Table 3 provides an overview of the DC COOKS with Heart cooking intervention sessions.

**Table 3 Tab3:** D.C. COOKS with Heart cooking intervention

Goal	Deliver cooking behavior intervention in a community setting
Type	In-person, chef-led instruction
Duration	6-week intervention with weekly 2-h sessions
Structure of sessions	Introduction and discussion of recipes and ingredients Cooking of recipes in groups Shared meal experience
Assessments	Semi-structured interviews (phone administered) Treatment fidelity Behavior change taxonomy (BCT)

### Intervention curriculum

Dietary outcomes from community cooking interventions have focused on adherence to those diet patterns related to cardiovascular health, Mediterranean diet or DASH diet. The Mediterranean diet is a dietary pattern known to reduce CV disease and mortality risk [40], presumably due to promotion of higher monounsaturated fat, fruit, and vegetable consumption. Moreover, cooking is reported as an important component of sustaining the Mediterranean diet [41]. The "Health meets Food" curriculum from the Goldring Center for Culinary Medicine (GCCM) will be used for the intervention. This longitudinal six-module curriculum is focused on the use of cooking skills to prepare foods from the Mediterranean diet. GCCM educates patients from the community in nutrition information for immediate and long-term social capital development by hands-on cooking and nutrition education [42]. The curriculum was created from prior evidence-based curricula surrounding preventive nutrition. At each session, learning objectives stem from the standard GCCM curriculum on the Mediterranean diet and nutrition education needed to start or maintain the diet. Food groups and principles of the Mediterranean diet, which include consumption of fruits and vegetables, nuts, seafood, and poultry, are highlighted in each session. The curriculum translates the Mediterranean diet for culture-specific kitchens across different socioeconomic levels [42]. In this manner, the participants are introduced to relatable food items that fall within food group categories of the Mediterranean diet. Table 4 shows a list of cooking sessions with topics, potential recipes, and study evaluation measures.

**Table 4 Tab4:** Cooking intervention sessions with topics, potential recipes, and study evaluation measures per session for D.C. COOKS

Session/Lesson	Topic	Potential recipes	Study evaluation measures collected
1	Mediterranean diet: Introduction to cooking and reading recipes	Salad with red wine vinaigrette and whole grain spaghetti with meat and lentils	Cooking diaries Grocery receipts
**2**	Macronutrients: dairy, breakfast, and understanding nutrition labels	Spinach and Cheese frittata Oat pancakes	Cooking diaries Grocery receipts
**3**	Vegetables: portion sizes and lunch	One pot bean chili and tomato and cucumber salad	Cooking diaries Grocery receipts Semi-structured interview
**4**	Legumes: good shopping habits and delectable dinners	Black bean burgers with balsamic marinated mushrooms	Cooking diaries Grocery receipts
**5**	Carbohydrates and snacks	Coconut pecan date rolls and fudgy black bean brownies	Cooking diaries Grocery receipts
**6**	Fats and cholesterol	Honey mustard pork tenderloin, savory braised collard greens and strawberry salad with honey lime vinaigrette	Cooking diaries Grocery receipts Semi-structured interview

Mediterranean diet-adapted recipes in the culinary education “Health meets Food” curriculum have been utilized within a racial/ethnic and economically diverse community in the Southern U.S. In a randomized controlled trial utilizing the curriculum, a primarily African-American (75%) type 2 diabetic population showed a reduction in hemoglobin A1c up to 6 months post the intervention [43]; with 46% of the study population living in a food desert. The GCCM curriculum is also reflective of the principles of food agency [17, 44], in that participants prepare their ingredients to *mis en place* standard, work cooperatively in pairs, conversation and comparison is encouraged among pairs, and a meal is shared to engage in sensory evaluation and future meal planning. During the first session, participants will receive kitchen safety orientation provided by the chef following standard curriculum kitchen safety guidelines.

In the current protocol, recipe selection will occur in conjunction with the study team and chef interventionist along with suggestions from community members who participate in phase 1. Barriers around food sourcing that may be a result of the neighborhood food environment or location will be discussed, and when possible food sourcing for recipes will come from locations within the community.

Each intervention will consist of a discussion of a nutrition topic and of related recipes, as well as updates from prior classes including any meals/recipes made by the participants’ at home. Participants will then work in groups of three to four to prepare assigned or selected recipes. During the process of cooking the recipes, the interventionist (chef) and culinary medicine, trained medical students will assist participants with instructions or techniques, if needed. Following the cooking process, a shared meal will occur in which each group will discuss what they cooked and the interventionist/students will be available for any questions. Final clean-up of the kitchen space will occur after the shared meal.

### Intervention assessments

During the six intervention sessions, individualized semi-structured interviews will occur with participants at the mid-point (3 weeks) and end-point of the intervention (6 weeks). Responses to interviews will be used to help assess feasibility, and mechanisms of cooking behavior. Interviews maybe administered by phone to participants. At the conclusion of the intervention, the semi-structured interview will also include exit interview questions regarding the intervention only. Research staff will take field notes at all intervention sessions to evaluate treatment fidelity, delivery of information, and culinary education. In addition, intervention characteristics such as hands-on activity time versus lecture/listening time will be recorded for each session.

Following the principles set forth by the NIH Science of Behavior Change Program [45], interventions to change health behaviors ought to be guided by a mechanisms-of-change hypothesis. A recent review of cooking interventions by Hollywood et al. [21] found several key behavior change techniques that may contribute to dietary changes from cooking interventions: (1) information on how to perform the behavior; (2) prompt practice (prompting a person to carry out a practical task related to cooking skills or cooking behavior once or numerous times); and (3) information on the consequences of the behavior tailored to the individual [21]. As noted by identified gaps in the literature, none of the reviewed interventions measured cooking behavior as an outcome. Therefore, behavioral mechanisms for cooking behavior within cooking interventions still need to be identified. Within our study, research staff will evaluate the behavioral change techniques present in the intervention design and those presented by participants within semi-structured interviews during the cooking intervention and during post-intervention clinic follow-up visits. The rubric for the behavioral change techniques will follow those of the Coventry, Aberdeen, and London-Refined (CALO-RE) taxonomy [46] as revised by Hollywood et al [21] (Fig. 2).

**Fig. 2 Fig2:**
[figure not shown]
Conceptual model of potential relationships between primary and secondary outcomes

## Study outcome measures

### Primary outcomes

The primary outcomes for this study are feasibility measures, home cooking behavior, and objective evaluation of cooking motor and process skills. In order to determine feasibility of the cooking intervention, we are collecting information on number of screened participants, number of participants enrolled, attendance at intervention sessions, and attrition rates. Attendance will be taken at each session. At a minimum, participants are counted as an attendee when one full intervention session has been completed. Completers of the intervention will be defined as participants who complete all six intervention sessions. Dropouts for the study will be defined as those who attend the first clinical visit, but do not attend any intervention session by the date of the final session. Attrition rates will be determined from the number of participants who stopped participating divided by the average number of participants at each time point, and over the total study period (see Fig. 4 for time points). We anticipate that our attrition rates will be at or below 33%, which is the reported attrition rate for this target population based on members of the research team’s experience recruiting from wards 7 and 8 [34]. Feasibility success will be achieved if the majority of participants (> 50%) reach 50% participation (3/6 sessions). This is based on two reports in the literature of cooking intervention studies among African-Americans in which this attendance metric was met [13, 15]. Information collected on feasibility and cooking behavior and skills will allow for appropriate sample size calculations for future studies.

Cooking behavior will be determined through multiple variables to provide a convergence of data. Using paper cooking diaries, participants will be instructed to start daily recording of home cooking following the initial clinical visit and will stop after the last visit, for a total collection time of 18 weeks. The design for the cooking diaries is fixed-schedule (once per day). Each daily entry will consist of marking the frequency of cooking at home, as well as commenting on enjoyment, interest [47], and perception of cooking skills.

Figure 3 illustrates the questions and answer choices for each cooking diary entry. At each clinical visit (TP0, TP2, TP3), additional measures of cooking behavior will be collected. Home cooking frequency, family meal behavior, and frequency of purchasing foods outside of the home over the prior 7 days will be determined using standardized national survey questions [48, 49]. Self-efficacy for cooking and food agency will be determined from validated survey tools [14, 44]. Psychosocial determinants of cooking will be assessed with a survey tool pre-tested within the target community by our team [50].

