Attrition	Number of participants that complete the study	Attrition will be based on the number of participants at the start and remaining at the end of the study, as well as at each time point. Attrition rates will be determined from the number of participants who stopped participating divided by the average number of participants at each time point, and over the total study period
Attendance	Attendance record at each intervention session using study log	Attendance will be taken at each intervention session and rates will be analyzed to determine the desired dosage (how much, how often and at what interval) for each participant by their characteristics
Participant burden	Observations of research team and participant feedback	Participant burden will be determined by data collection assessments, research team’s perception of participants’ understanding of questions and data collection methods, and if participants respond with missing or unusable data. The study team will also assess if participants have enough time and capacity to complete data collection procedures.
Treatment fidelity [54]	Guidelines for treatment fidelity from the NIH Behavior Change Consortium workgroup on treatment of fidelity	Treatment fidelity assessment grid will be used to determine implementation of the intervention. Cooking diaries and interviews will also be used as a measure of implementation/intervention fidelity.
Secondary outcomes		
Social network index [55, 56]	Self-administered 12 item measure	SNI is a self-administered 12-item instrument that assesses participation in 12 types of social relationships. There are three measures within the SNI: number of high-contact roles (network diversity), number of people in social network, and number of embedded networks.
Health promoting Lifestyle Profile II (HPLP-II) [57]	Self-administered 52-item instrument	The HPLP-II is a self-administered 52-item instrument that measures the frequency of self-reported healthy behaviors. It consists of 6 subscales: physical activity, spiritual growth, health responsibility, interpersonal relations, nutrition, and stress management (including sleep quality).
Perceived stress [58]	Perceived stress scale (PSS) is a self-administered 10 item instrument	PSS measures an individual’s perceptions about the nature of events and their relationship to coping resources of that individual. This 10 item tool uses a 5 point Likert scale for each item.
Neighborhood factors		

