### Quantitative data

#### Sample size justification

For phase 2, sample size justification was done in accordance with Billingham et al. [70]. From the literature for published cooking interventions, intervention group size ranges from 12 to 30 participants [13–15, 43]. We therefore selected a sample size of 30 participants for phase 2. We also based the sample size on expected attrition. From our previous community study (NCT 0192778 [34];), we anticipate a 33% attrition rate for the first clinical visit. Therefore, in order to reach 30 participants, we plan to screen 45 participants*.*

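### Attrition is defined as leavers over the average headcount, which overstates the proportion lost and is not on the scale of the 33% expectation

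*Protocol article*

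**What the plan says.** Attrition is one of the feasibility measures among the primary outcomes. The Primary outcomes section of the protocol article gives the formula: "Attrition rates will be determined from the number of participants who stopped participating divided by the average number of participants at each time point", and extends it to the whole study period. It then sets an expectation: "We anticipate that our attrition rates will be at or below 33%, which is the reported attrition rate for this target population".

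The Attrition row of Table 5 opens with what sounds like a start-to-end comparison, "Attrition will be based on the number of participants at the start and remaining at the end of the study", and then repeats the average-headcount formula. It does not make the starting number the denominator.

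Sample size justification uses 33% as well, but for one particular stage: "we anticipate a 33% attrition rate for the first clinical visit". From this it concludes that "in order to reach 30 participants, we plan to screen 45 participants".

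Study procedures says that the intervention begins only after all baseline visits are done, with those who completed one. The article describes no later entry and no replacement.

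**The concern.** Dividing leavers by the average number present gives a turnover-type or mid-period rate. It is not the proportion of a cohort that was lost. In a closed cohort the two differ as soon as one person leaves, always in the same direction for the whole-study figure, and the gap widens as losses grow. A reader who sees an attrition rate beside an expected 33% will take both as proportions of those who started.

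At stake is the accuracy of a reported primary feasibility figure. The article says that the feasibility information will support sample size calculations for future studies. The usual inflation, N/(1 − d), needs d to be a proportion of starters, so an inflated d carries straight into the next trial's recruitment number.

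**Working it through.** **Inputs.** 30 participants in phase 2, 45 to be screened, and 33% attrition (Sample size justification); leavers over average headcount (Primary outcomes and Table 5); closed cohort (Study procedures); four time points, TP0 to TP3 (Study design).

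**1. Reproduce the plan's own figure.** With 33% as a proportion of those who start, N/(1 − d) = 30/(1 − 0.33) = 30/0.67 = 44.8, rounded up to 45. This matches the article, and 15/45 = 33.3%. So the sample size treats 33% as a start-based proportion. Under the attrition formula the same loss would be 15/((45 + 30)/2) = 15/37.5 = 40.0%. If the 33% were average-based, the start-based loss would be 0.33/(1 + 0.165) = 28.3%, and 30/(1 − 0.283) = 41.9, so 42 screened would do. The stated 45 does not fit that reading.

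**2. Direction.** In a closed cohort the headcount can only fall, so any average that includes a later, smaller count is below the starting number. The whole-study ratio therefore exceeds the proportion lost on either reading of the average.

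**3. Size, average of start and end.** For L lost of 30, compare L/30 with L/((30 + 30 − L)/2).

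| Lost | Over starters | Over average |
|---|---|---|
| 3 | 10.0% | 3/28.5 = 10.5% |
| 6 | 20.0% | 6/27 = 22.2% |
| 8 | 26.7% | 8/26 = 30.8% |
| 9 | 30.0% | 9/25.5 = 35.3% |
| 10 | 33.3% | 10/25 = 40.0% |
| 15 | 50.0% | 15/22.5 = 66.7% |

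The ratio passes 100% when L > (60 − L)/2, that is, when L > 20.

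**4. Size, average over four time points.** The wording also allows this reading. For 10 lost of 30:

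- all late (30, 30, 30, 20): 10/27.5 = 36.4%
- spread (30, 27, 23, 20): 10/25 = 40.0%
- all early (30, 20, 20, 20): 10/22.5 = 44.4%

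The same ten losses give three different figures, all above 33.3%.

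**5. Interval rates.** On the spread path, with each interval's own start/end average, the three rates are 3/28.5 = 10.5%, 4/25 = 16.0% and 3/21.5 = 14.0%. Over those present at each interval's start they are 3/30 = 10.0%, 4/27 = 14.8% and 3/23 = 13.0%. If the whole-study average of 25 were used for the last interval instead, 3/25 = 12.0% would fall below 13.0%. The overstatement is therefore certain for the whole-study figure, while the interval figures depend on which average is meant.

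**6. Stage.** The 33% in Sample size justification covers loss from screening up to the first clinical visit (45 to 30). Primary outcomes sets 33% against attrition at the study time points and over the whole study. These are different losses with different starting groups, so the figures would not be comparable even with a common denominator.

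**The case against.** The strongest reply is that nothing is decided by this number. The 33% is what the investigators anticipate. The only success criterion is that more than half of participants attend at least 3 of 6 sessions, and it does not use the formula. Neither does the 45, which reproduces correctly. Leavers over average number present also has the form of a central rate, which can be used in closed cohorts, so the article contains no slip in calculation. The counts needed for a start-based proportion are to be collected anyway. At low loss the gap is small, about 0.5 points at 10%.

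Most of this stands, and it limits severity. A reader might infer that the trial would be judged to have failed a target; the documents do not support that. On the start/end average with 33% read literally, only 9 lost changes side. Ten lost also does if 33% means one third. On the four-time-point average, nine late losses (30, 30, 30, 21) give 9/27.75 = 32.4% and do not change side. Values above 100% need more than 20 of 30 lost, far beyond what the article expects.

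A reader might also infer from "Dropouts for the study will be defined as those who attend the first clinical visit, but do not attend any intervention session" that someone who attends once and never returns escapes the attrition count. That does not follow. The attrition numerator is those who stopped participating, not those labelled dropouts, and the article counts anyone who completes one full session as an attendee. The dropout label is a separate matter.

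The reply does not remove the main point. The article states the denominator twice, for a primary measure, and puts the result beside a 33% that its own sample size uses on another scale and for another stage. How the cited earlier study calculated its 33% cannot be seen.

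**Conclusion.** The point holds as a should-fix correction to a reported primary feasibility figure. As defined, whole-study attrition overstates the proportion lost: by 5.3 points at 9 of 30 (35.3% − 30.0%) and by 6.7 points at 10 of 30 (40.0% − 33.3%) on the start/end average, and by 3.1 to 11.1 points at 10 of 30 on the four-time-point average. It is not on the same scale as the 33%, and that 33% is tied to two different stages in two sections.

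This rests on three assumptions: 30 starters, no entry after baseline (from Study procedures), and a start-based 33% (inferred from the 45-to-30 calculation, since the source is not shown). It does not affect the success rule, the phase 2 sample size or the number to be screened. As an illustration of the later effect, with 100 evaluable participants assumed for a future trial, a true loss of one third needs 100/(2/3) = 150 recruited, whereas the reported 40% would give 100/0.60 = 167.

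**What to change.** In Primary outcomes and in the Attrition row of Table 5, replace the average-headcount formula with:

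- **Cumulative attrition at a time point:** the number who have permanently stopped participating by then, divided by the number who completed TP0.
- **Interval attrition:** the number who stopped during the interval, divided by the number still participating at its start.
- **Screening-to-baseline loss, reported separately:** (screened − completing TP0)/screened.

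Then state, in both Primary outcomes and Sample size justification, which of these the 33% refers to. Changing the denominator alone would not make the figures comparable, because a rate that starts at TP0 excludes the loss before the first clinical visit.

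The numerator should stay with permanent stopping and not absence from a visit. Otherwise a participant who misses TP2 and returns at TP3 would be counted as lost and then regained, and cumulative attrition could fall.

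The cost is a few sentences in three places. No data collection changes: screening, enrolment, attendance and numbers remaining at each time point are already planned.

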### Study procedures

In phase 1 of this study, participants (*n* = 20) will take part in one of two moderated focus groups designed to explore participants’ experiences with food and dietary selections and cooking behavior. Within this phase, participants will also take self-administered surveys related to cooking behavior, non-dietary health behaviors, and psychosocial factors. Open-ended (qualitative) questions for the focus groups were selected to elicit feedback regarding facilitators and barriers to cooking and perceptions about the feasibility of the intervention regarding (1) obtaining food for cooking, (2) use of cooking skills, (3) social norms around home cooking, (4) personal attitudes and knowledge, (5) preferences for recipes/food choice, and (6) preferences for intervention timing. Focus group feedback will also be used to modify the survey, if needed. Data analysis is anticipated to occur over a 1-month time period and the results of data analysis will inform the second phase. Specifically, the data captured from this phase will inform phase 2 in terms of recipe selection for intervention, local locations to source food for the intervention, anticipated concerns about intervention location, and schedule of sessions.

Phase 2 of the study consists of two parts: clinical visits, surveys, and interviews at pre (TP_0_) and post intervention intervals (TP_2_, TP_3_) and the cooking intervention (TP_1_). We will recruit thirty (*n* = 30) participants for this phase. Phase 2 will start with a baseline visit (TP_0_) prior to the intervention start. During this visit, a clinical history and physical examination, objective cooking assessment, dietician interview, and phlebotomy for CVD biomarkers will take place. Following completion of baseline visits for all participants, the community intervention will start with all participants who have completed the initial clinical visit. We estimate that it will take 4 weeks for all participants to complete their baseline visit. Participants will return for the second clinical visit at 6 weeks and 12 weeks post the intervention. To ensure that time of participation and days of follow up in the study are equal among participants, those who enroll and come in for their baseline visit at the earliest time point (week 4) will return for follow up visits prior to participants who completed baseline visits closer to the end of the initial time point (T_0_).

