**Fig. 4 Fig4:**
[figure not shown]
The planned flow and steps of data collection within phase 2 relevant to expected recruitment and retention

Retention efforts focused on participant engagement include reminder phone calls to participants on a weekly basis during the intervention and 1 week and 1 day prior to all clinical visit appointments. Participants will be discontinued from the study if any of the following should occur: participant requests to be removed from the study, participant does not participate in the initial clinical visit, or participant is unable to participate in the intervention component.

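### The feasibility success rule does not say whether non-attenders and discontinued participants stay in its denominator, and the discontinuation rule ends data collection on them

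*Protocol article*

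**What the plan says.** All references are to the protocol article.

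- **Primary outcomes**, success rule: "Feasibility success will be achieved if the majority of participants (> 50%) reach 50% participation (3/6 sessions". The group meant by participants is not specified.
- **Primary outcomes**, categories: "participants are counted as an attendee when one full intervention session has been completed". Completers attend all six sessions. "Dropouts for the study will be defined as those who attend the first clinical visit, but do not attend any intervention session", judged at the date of the final session. None of these categories is tied to the success rule.
- **Primary outcomes** and **Table 5**, attrition: its denominator is an average of the numbers present over time. This is given for attrition only.
- **Study procedures**: 30 people are to be recruited for phase 2, and "the community intervention will start with all participants who have completed the initial clinical visit".
- **Sample size justification**: "We therefore selected a sample size of 30 participants for phase 2", and "in order to reach 30 participants, we plan to screen 45 participants". The same word thus covers people screened and people enrolled.
- **Recruitment and retention plan**: the grounds for discontinuation from the study are the person's own request and the following two: "participant does not participate in the initial clinical visit, or participant is unable to participate in the intervention component". No timing is given, and nothing is said about how such people count in the attendance result.

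**The concern.** Feasibility is a primary outcome, and people who enrol but cannot get to the classes are the most direct evidence against it. Two parts of the plan bear on them, and neither refers to the other. The success rule leaves its denominator open. The discontinuation rule takes people who cannot take part in the intervention out of the study altogether. An analyst who takes participants to mean those still in the study, or those who attended at least once, would drop these people from the rate. Everyone dropped in this way is likely to have missed the three-session mark, so the error runs in one direction, towards success.

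There is also a loss of information. The phase 2 primary aim in Table 1 links feasibility to facilitators of and barriers to cooking. Discontinuation read literally ends the two follow-up clinical visits, the diaries and the later interviews for the people who met the greatest obstacles to taking part.

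**Working it through.** **Inputs.** Planned phase 2 size 30, number screened 45, and 33% loss at the first clinical visit (Sample size justification). Success if more than 50% reach 3 of 6 sessions, and attrition expected at or below 33% (Primary outcomes). The number of non-attenders left out is an assumption, so a range is shown.

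**The plan's own figure.** 30 / (1 − 0.33) = 44.8, rounded up to 45. The stated 45 reproduces. It concerns loss before enrolment and does not settle the denominator of the success rule.

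**Pass mark by denominator.** With k non-attenders left out, the denominator is 30 − k, and the pass mark is the smallest whole number above (30 − k)/2.

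| Left out (k) | Denominator | Needed | Needed as % of 30 |
|---|---|---|---|
| 0 | 30 | 16 | 53.3% |
| 3 | 27 | 14 | 46.7% |
| 6 | 24 | 13 | 43.3% |
| 8 | 22 | 12 | 40.0% |
| 10 | 20 | 11 | 36.7% |

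The same data can therefore give either answer. Twelve people reaching three sessions is 12/30 = 40.0% (not met) or 12/22 = 54.5% (met). Eleven is 11/30 = 36.7% (not met) or 11/20 = 55.0% (met).

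**Chance of declaring success.** Let X be the number of the 30 who reach three sessions, X ~ Binomial(30, p), with p the true share among all enrolled. With the denominator fixed, success is X ≥ 16. With 10 non-attenders left out, it is X ≥ 11.

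| True p | All 30 counted | 10 left out |
|---|---|---|
| 35% | 0.03 | 0.49 |
| 40% | 0.10 | 0.71 |
| 45% | 0.23 | 0.87 |
| 50% | 0.43 | 0.95 |

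In a second version each person is removed at random with overall probability 10%, 20% or 33%, all removals falling among those not reaching three sessions. At a true 40%, the chance of success is then 0.25, 0.46 or 0.78, against 0.10 with nobody removed.

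**What discontinuation loses.** Table 2 places data collection after the start of the classes as follows: interviews at weeks 3, 6, 12 and 18, clinical visits with surveys and dietary assessment at weeks 12 and 18, the repeat cooking skill assessment at week 12, and daily diaries through week 18. Whatever falls after the date of discontinuation is lost. The baseline interview, surveys and skill assessment, and the phase 1 focus groups, are not affected.

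**The two rules side by side.** A person with no session attended is classed as a dropout only once the last session has passed. A person unable to take part can be discontinued at an unstated time. Someone who enrols and then cannot attend could fall under both, and the article does not say which applies or how either is counted.

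**The case against.** The best defence is that the wording already points to everyone enrolled. The rule says participants and not attendees, and the same paragraph uses attendee, completer and dropout as subsets of participants. Study procedures starts the intervention with everyone who completes the baseline visit. People with no session are named and counted as dropouts, so they would be visible in the report. The discontinuation rule concerns conduct, and leaving follow-up is not the same as leaving an attendance rate. Being unable to take part is also not the same as not turning up. Most of this stands: no sentence removes anyone from the denominator. But no sentence keeps them in either, and the article itself states the threshold, the categories and the discontinuation rule without connecting them.

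A reader might infer three stronger things that the article does not support.

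- *That the plan excludes non-attenders from the rate.* It permits this but does not prescribe it.
- *That the threshold decides whether a larger trial goes ahead.* It is the only numeric success mark, but no progression decision is tied to it. Attrition, participant burden and treatment fidelity are feasibility measures as well, and the stated use of the information is sample size calculation for future studies.
- *That the barrier data are deleted.* Phase 1 and baseline data survive, and interviews may be done by phone. The loss is of later data on the people discontinued.

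An analysis plan or the full protocol may define the analysis set. That lowers the weight of the point, but the interaction of the rules printed here would still need to be settled.

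**Conclusion.** The point holds as an ambiguity that can bias the result in one direction, and it is cheap to remove. If non-attenders are left out, the share of enrolled people needed for success falls from 53.3% to between 46.7% (3 left out) and 36.7% (10 left out). At a true 40%, the chance of declaring success rises from 0.10 to 0.71 in the case of 10 left out.

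These sizes rest on assumptions: 30 people complete the baseline visit, participants behave independently, and those left out would not have reached three sessions. Nothing in the article forecasts 8 or 10 non-attenders. Ten of 30 is the upper end suggested by the general expectation of attrition at or below 33%, whereas the 33% used for sample size is loss at the first clinical visit. If the sponsor already intends all enrolled people to count, the rate is sound and only the wording needs to say so.

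The loss of follow-up data under the discontinuation rule is a separate and more moderate matter, limited to data after baseline.

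**What to change.** 1. **Primary outcomes.** State that the denominator of the success rule is all participants who complete the baseline clinical visit, that dropouts and discontinued participants count as not reaching three of six sessions, and that any rate among attendees only is supplementary. Fix this before attendance is known.
2. **Recruitment and retention plan.** Reconcile the ground "participant is unable to participate in the intervention component" with the dropout definition, so that being unable to attend classes does not by itself end data collection (the two follow-up visits, diaries and phone interviews) unless consent is withdrawn.
3. **Optional.** Report the proportion with an exact 95% confidence interval. At the pass mark of 16/30 the Clopper-Pearson interval is 34% to 72%, which shows how little a bare pass establishes. This is secondary to the denominator.

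The cost is a wording change in two paragraphs, some effort to follow non-attenders within visits already planned, and a success rate that may come out slightly lower.
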